### Stage 2b. ENDOCELL Working Group (expert panel)

An additional task of the steering committee will be to define the ENDOCELL Working Group, the panel of experts who will be invited to complete the online ENDOCELL survey(s). The ENDOCELL Working Group will be compiled based on a combination of purposive sampling and literature review-based sampling. PubMed will be searched for all papers published in the last 10 years describing the use of cells/*in vitro* systems. Search terms will be (endometriosis OR endometrium) AND (primary cells OR cell line OR organoid OR* in vitro*) NOT (review). This search will be performed prior to launching the ENDOCELL survey specific to each methodology. First and last authors of the papers will be identified as potential members of the ENDOCELL Working Group and duplicate names/authors will be excluded. The generated list of experts will be evaluated by the ENDOCELL steering committee who will prioritise the identified experts according to their suitability in participating to the survey. The steering committee can also add further names. Members of the ENDOCELL Working Group will be recruited from both academic and industrial sectors.

Depending on the methodology/survey, 150–300 ENDOCELL Working Group members will be invited to participate in the survey. Individuals who wish to opt out of the survey will be removed from subsequent invitations. Participants will be blinded to identities of other individuals in the group, and they will not know the specific answers that other individuals provide. The dropout rate based on previous Delphi studies cannot be foreseen in advance given the wide range reported (20–60%) in the literature (Vogel *et al.* 2019, Mendoza *et al.* 2022).

### Stage 2c. Participation to the ENDOCELL survey eDelphi rounds 1, 2 and 3

The ENDOCELL Working Group members will be invited to participate in the survey via a personalised email that explains the objective, the methodology and timelines of this eDelphi protocol. The present protocol (or an extract of it) plus a short video tutorial will also be provided. The ENDOCELL Working Group will be asked to complete three rounds of the eDelphi. They will have a 4-week period to complete each round of the ENDOCELL survey online. In the first eDelphi round, the ENDOCELL Working Group will be also encouraged to add any missing topics/outcomes/questions using the free-text option (Colonna *et al.* 2017, Isidori *et al.* 2019, Vogel *et al.* 2019, Brown *et al.* 2021). The ENDOCELL steering committee will also complete the survey. Each participant in the survey will be assigned a unique identifier to anonymise their responses. Following the first eDelphi round, the ENDOCELL facilitators will analyse the data, identify new items suggested by the ENDOCELL Working Group, and modify the ENDOCELL survey if necessary. The complete ENDOCELL steering committee will be involved in final approval of the new version of ENDOCELL survey that will comprise the identical list of propositions from the previous survey version, plus the newly identified items/procedural steps and corresponding formulated propositions (Fig. 1).

The new ENDOCELL survey will be sent to the ENDOCELL Working Group (eDelphi round 2) together with the results of the first survey round. Results will be visualised in an anonymous manner by each panellist together with their own response from the previous survey round. Participants will be asked to reconsider their responses in light of the anonymised Working group’s responses. Results of the ENDOCELL survey round 2 will be analysed, and a third eDelphi round will be performed (Fig. 1).

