To remedy this situation, the ENDOCELL-Seud (indicated as ‘ENDOCELL’ in the rest of the study) project was designed to solicit expert opinions to determine the validity of different methods used to isolate, culture and characterise primary cells from endometrium, endometriosis and adenomyosis and to establish SOPs (Sinha *et al.* 2011). The ENDOCELL project is based on the Delphi method, an iterative investigation method, which, through a series of evaluation stages aims to bring together the most comprehensive opinion, shared in single statements. The tool is commonly used when a consensus on a specific topic needs to be obtained to fill the gap due to the absence of SOPs or guidelines (Coticchio *et al.* 2021, Braungart *et al.* 2022, Hohmann 2022). The ENDOCELL project aims to provide clear guidance to researchers on unbiased *in vitro* methodologies to further the field of reproductive science. The protocol to harness the opinion of experts and to arrive at consensus opinions on the topics debated is described herein.

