### Stage 1. Identification of methodologies and items to harmonise

The first stage in the ENDOCELL project was to define the *in vitro* methodologies in endometrial research needing harmonisation. The ENDOCELL steering committee identified 11 methodologies for which a consensus is lacking, that is, the establishment and maintenance of (1) primary endometrial cells, (2) normal endometrial cell lines, (3) primary endometriotic cells, (4) primary adenomyotic cells, (5) primary myometrial cells, (6) endometriotic cell lines, (7) epithelial organoids, (8) epithelial and stroma organoid (assembloids), (9) spheroids, (10) 3D culture and cell printing, (11) progenitor stem cells, (12) uterine/endometrial-specific endothelial cells and (13) uterine/endometrial-specific immune cells (Table 1). Subsequently, the steering committee will define items in the methodologies that vary across laboratories. The identification and selection of these items will be guided by the expertise of the committee members together with the outcome of a recent systematic review conducted by the ENDOCELL facilitators, which highlighted critical steps in commonly used *in vitro* procedures (Romano *et al.* 2020). In addition, in compliance with similar initiatives in clinical research (Williamson *et al.* 2017) and translational/basic research (Taylor *et al.* 2008, Bustin *et al.* 2009), the following guiding principles will be considered when evaluating items to be included: (i) reporting of the item should facilitate reproducibility of the studies (i.e. readers should be able to replicate the findings based on the information reported such as culture media and supplements), identifying steps in *in vitro* procedures that influence reproducibility; (ii) reporting of the item should facilitate assessment of the quality of the study and risk of bias, allowing avoidance of experimental errors (i.e. temperatures and timing between tissue collection and culture, phenotypic characterisation of cultures, set of required biomarkers and functional features to ensure cell lineage characterisation and if needed subpopulation definition), (iii) a minimum set of items will be determined for reporting in studies employing cell cultures derived from eutopic and ectopic endometrium, ensuring adherence to data governance standards (i.e. requirements of minimal patients’ data).

**Table 1 tbl1:** Methodologies and items to be harmonised in the ENDOCELL project.

Methodologies	Items	Procedural steps

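### The literature search that finds panel candidates has no adenomyosis or myometrium term, so the panels for those two methodologies may under-represent the relevant experts

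*Protocol article*

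**What the plan says.** Stage 2b builds the expert panel from two sources, purposive sampling and a PubMed search over the last 10 years. The article introduces the string as fixed, "Search terms will be (endometriosis OR endometrium) AND (primary cells OR cell line OR organoid"; through to its end it reads "endometriosis OR endometrium) AND (primary cells OR cell line OR organoid OR* in vitro*) NOT (review". On its use the article says: "This search will be performed prior to launching the ENDOCELL survey specific to each methodology". Only this string is given, with no variant for any methodology.

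The search yields people through authorship: "First and last authors of the papers will be identified as potential members of the ENDOCELL Working Group". The steering committee then ranks the resulting list by suitability and may add names. Each survey invites 150–300 people.

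On scope, the Introduction sets out to judge methods for "primary cells from endometrium, endometriosis and adenomyosis and to establish SOPs". Stage 1 and Table 1 list 13 methodologies (the text elsewhere counts 11; this point uses the list). Among them are "4) primary adenomyotic cells, (5) primary myometrial cells". The Figure 1 caption describes the working group as being defined for the particular methodology.

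**The concern.** In a Delphi study the panel is the sample, and the search is the part of the sampling plan that depends least on whom the organisers already know. If the string does not name a tissue, groups that publish only on that tissue are missed, and the panel for that survey leans towards endometrium and endometriosis authors.

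Two features of the plan raise the stakes. First, the consensus rule in Stage 3 counts the neutral rating (3) with the agreeing ratings towards the 70% threshold. Panellists with little experience of a method who answer neutrally would add to positive consensus, so a poorly matched panel need not show up as a lack of consensus. Second, the Introduction itself criticises work that applies endometrium protocols to ectopic lesions. Standards for adenomyotic or myometrial cells set mainly by endometrium authors would risk a similar transfer.

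**Working it through.** There is no sample-size or error-rate figure to reproduce. The check sets the string against the list of methodologies, term by term.

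**Inputs**
- Tissue bracket (Stage 2b): endometriosis, endometrium.
- Culture bracket (Stage 2b): primary cells, cell line, organoid, *in vitro*.
- Rule: a paper must satisfy both brackets.
- Methodologies: the 13 entries in Stage 1 and Table 1.

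| No. | Methodology | Tissue term in the string | Culture term in the string |
|---|---|---|---|
| 1 | Primary endometrial cells | endometrium | primary cells |
| 2 | Normal endometrial lines | endometrium | cell line |
| 3 | Primary endometriotic cells | endometriosis | primary cells |
| 4 | Primary adenomyotic cells | **none** | primary cells |
| 5 | Primary myometrial cells | **none** | primary cells |
| 6 | Endometriotic lines | endometriosis | cell line |
| 7 | Epithelial organoids | no tissue in label | organoid |
| 8 | Assembloids, labelled as organoids | no tissue in label | organoid |
| 9 | Spheroids | no tissue in label | generic only |
| 10 | 3D culture and printing | no tissue in label | generic only |
| 11 | Progenitor stem cells | no tissue in label | generic only |
| 12 | Endothelial cells | endometrial part only | generic only |
| 13 | Immune cells | endometrial part only | generic only |

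**Tissue bracket.** Methodologies 4 and 5 name a tissue for which the string has no term: 2 of 13. Because of the AND, a matching culture term does not help. A paper on myometrial cells is retrieved only if it also mentions endometrium or endometriosis. Let *p* be the share of relevant papers that mention neither. The share lost is then *p*. The documents give no retrieval counts, so *p* could lie anywhere from 0 to 1 for each tissue.

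The two tissues are probably not equally exposed. The Introduction describes adenomyosis as one form of ectopic endometrial implant, so papers on it will plausibly often mention endometrium or endometriosis. No such link is stated for myometrium, which is therefore the clearer gap.

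**Culture bracket.** Methodologies with a term of their own: 4 (nos. 1, 3, 4, 5) + 2 (nos. 2, 6) + 2 (nos. 7, 8) = 8. Without one: 13 − 8 = 5 (nos. 9–13). Three of the five are "9) spheroids, (10) 3D culture and cell printing, (11) progenitor stem cells"; the others are endothelial and immune cells. Assembloids are not among them, because the label contains the word organoid: "7) epithelial organoids, (8) epithelial and stroma organoid (assembloids". All five can be reached through the general term *in vitro*, so they lack a dedicated term but are not shut out.

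**Do the later steps restore missed authors?**
- Ranking by suitability works on the list that the search produced. It cannot recover someone who was never on it.
- Purposive sampling and committee additions can recover missed experts. The article states them as an option, with no criterion or minimum number per methodology.

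**The case against.** The strongest defence is that the string only finds candidates and does not itself form the panel. It is broad by design, and it is followed by purposive sampling, ranking by suitability and optional additions by 12 scientists chosen for publication record and expertise. A general search followed by selection for each survey is a legitimate way to reach a methodology-specific panel. Adenomyosis papers will often be caught anyway, and myometrial cells lie at the edge of a project centred on eutopic and ectopic endometrium.

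Much of this stands, and it rules out three stronger readings that a reader might infer:
- *That the string omits most of the newer culture models.* It does not. *In vitro* follows organoid directly and can reach them, and organoid itself matches two of the four 3D models (nos. 7–10).
- *That panels for the affected methodologies will not include the people who use those methods.* The article provides routes by which they can be invited, so the supportable wording is that they may be under-represented.
- *That the literature-based half of the sampling is lost.* The article states no half-and-half split and gives no retrieval figures.

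What the defence does not remove is the mismatch itself. The string is stated as fixed, it serves every survey, and it names neither tissue. The correction depends on committee discretion without any rule per methodology.

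**Conclusion.** The point holds in a narrow form. For 2 of the 13 listed methodologies, the stated search has no term for the tissue under study, and one of those tissues is in the project's stated aim. Literature-based candidates for these two surveys may under-represent groups that publish only on adenomyosis or myometrium, with myometrium the clearer case. The committee's power to add names reduces the risk without closing it.

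The loss cannot be quantified. It depends on how many relevant papers mention neither endometrium nor endometriosis, on how PubMed maps the terms, and on how many names the committee adds; the documents show none of these. The view that adenomyosis is less exposed is an inference from the Introduction, not a count. For the five methodologies without their own culture term, the finding is only a possible loss of search sensitivity. Severity: should be fixed, before the affected surveys launch.

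**What to change.** Extend the tissue bracket to `(endometriosis OR endometriotic OR endometrium OR endometrial OR adenomyosis OR adenomyotic OR myometrium OR myometrial)` before the adenomyotic and myometrial surveys launch. The search is already repeated for each survey, so no new step is needed.

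As an optional further step, add a culture term specific to each survey where none exists: spheroid, 3D culture or bioprinting, stem or progenitor cell, endothelial cell, immune cell. Assembloid could be added for methodology 8, although organoid already matches its label.

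The cost is a longer author list for the committee to screen, in the four weeks that the Figure 1 caption gives to defining the working group. The Delphi rounds and the consensus rule do not change. Once a survey has closed, a poorly matched panel could be corrected only by repeating its rounds.

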### Stage 3. Data analysis and consensus grading

Data will be analysed by the ENDOCELL steering committee at the end of each eDelphi procedure. Results will be reported as median values of the 5-point Likert agreement scale for each procedural step/proposition in the survey. Consensus will be reached for each procedural step/proposition when the sum of choices 1, 2 and 3 (agree) or 4 and 5 (disagree) reaches 70%. No consensus is reached when the sum of the responses for a negative consensus or a positive consensus is <70%.

The strength of agreement will be measured by the mean absolute deviation from the median (MADM), that is, the average distance of the ratings of each participant from the median, and will be ranked as low (MADM > 1.41), moderate (MADM = 1.08–1.41) and high (MADM < 1.08) (Brown *et al.* 2021).

Stability of consensus at the end of the eDelphi procedure will be reached if the between round group responses varied by ≤10%.

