### Stage 2a. ENDOCELL surveys

The level of consensus for each procedural step/proposition will be expressed using a 5-point Likert scale (1 = strongly agree, 2 = somewhat agree, 3 = neither agree nor disagree, 4 = somewhat disagree and 5 = strongly disagree), which has already demonstrated consistent outcomes in previous Delphi studies (Akins *et al.* 2005, Vogel *et al.* 2019). A free-text box will be provided for general comments on each item (to justify agreements or suggest wording changes), and a free-text box will be provided at the end of the survey to suggest additional checklist items or provide general comments on the checklist (Colonna *et al.* 2017, Isidori *et al.* 2019). All surveys will be created and administered using Qualtrics (Provo, USA), a user-friendly, feature-rich web-based survey tool that complies to the privacy laws and General Data Protection Regulation.

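### The MADM cut-offs are miscalibrated for a 5-point scale: evenly scattered answers grade 'moderate', and 'low' is impossible under negative consensus and confined to near-polarised splits under positive consensus

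*Protocol article*

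**What the plan says.** Three parts of the protocol article bear on this.

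- **Scale** (Stage 2a, ENDOCELL surveys): "The level of consensus for each procedural step/proposition will be expressed using a 5-point Likert scale", running from 1 for strong agreement to 5 for strong disagreement.
- **Consensus rule** (Stage 3, Data analysis and consensus grading): consensus is declared "when the sum of choices 1, 2 and 3 (agree) or 4 and 5 (disagree) reaches 70" per cent.
- **Strength of agreement** (Stage 3): this is measured by MADM, "the average distance of the ratings of each participant from the median", and is "ranked as low (MADM > 1.41), moderate (MADM = 1.08–1.41) and high (MADM < 1.08".

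The cut-offs are attributed to a cited study. The article does not derive them or adapt them to the 5-point scale. It does not say whether the grade is given to every proposition or only to those that reach consensus.

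**The concern.** A strength grade is useful if its bottom level is what a panel with no common view would receive, and if all its levels can occur among the statements being graded. Ratings from 1 to 5 confine MADM to the range 0 to 2, and the 70% rule narrows that range further before any grade is read. Cut-offs as high as 1.08 and 1.41 may then leave the lowest grade empty and give unstructured answers the middle grade.

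What is at stake is the label attached to each published statement. The Recommendation document section plans to circulate the agreed recommendations to several societies for comment and endorsement. MADM is the plan's named measure of strength, so readers would take its label as the strength of each recommendation.

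**Working it through.** **Inputs.** All come from the protocol article: ratings 1 to 5 (Stage 2a); positive consensus if at least 70% are in 1–3, negative if at least 70% are in 4–5; MADM as the mean of |rating − median|; cut-offs 1.08 and 1.41 (all Stage 3). The cut-offs are cited without derivation, so they cannot be reproduced from the document. What can be checked is how they behave on this scale.

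**Formula.** With shares p1 to p5 and median m, MADM = Σ pk·|k − m|. The median minimises this sum. MADM is therefore no larger than the sum taken about any other point, and no larger than the average of two such sums.

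**1. Even scatter (20% in each category).** m = 3, MADM = (2 + 1 + 0 + 1 + 2)/5 = 1.20: *moderate*.

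The result survives sampling variation. Stage 2b says "150–300 ENDOCELL Working Group members will be invited to participate in the survey" and gives dropout of 20–60%. If dropout is applied once to the invited panel (an assumption), the number of raters runs from 150 × 0.4 = 60 to 300 × 0.8 = 240. In 20,000 simulated panels of each size, answering at random with equal probability in each category, the grades were:

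| Raters | *high* | *moderate* | *low* |
|---|---|---|---|
| 60 | 10.6% | 88.2% | 1.1% |
| 120 | 3.8% | 96% | 0.1% |
| 240 | 0.7% | 99% | 0% |

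**2. Negative consensus.** Let q be the share in 4–5. Average the sums about 4 and about 5. A rating of 4 or 5 contributes 0.5, and any other rating contributes at most (3 + 4)/2 = 3.5. So MADM ≤ 3.5(1 − q) + 0.5q = 3.5 − 3q. At q = 0.70 this is 3.5 − 2.1 = 1.40, and it falls as q rises. The bound is reached by 30/0/0/20/50: about m = 4, 0.30 × 3 + 0.50 × 1 = 1.40. Since 1.40 < 1.41, *low* cannot occur, whatever the panel size.

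**3. Positive consensus.** Let s be the share in 1–3. Average the sums about 1 and about 3. A rating of 1, 2 or 3 contributes 1, a 4 contributes 2 and a 5 contributes 3. So MADM ≤ s + 3(1 − s) = 3 − 2s. At s = 0.70 this is 1.60, reached by 50/0/20/0/30: about m = 2, 0.50 × 1 + 0.20 × 1 + 0.30 × 3 = 1.60. *Low* needs 3 − 2s > 1.41, that is s < 0.795. It is therefore excluded once the share in 1–3 reaches 79.5%. Among all distributions in 1% steps that meet the rule, every one graded *low* has at least 62% of raters at the two extremes.

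**4. What *high* admits.** With 74% at 1 and 26% at 5, m = 1 and MADM = 0.26 × 4 = 1.04: *high*. With 73%/27% it is 0.27 × 4 = 1.08: *moderate*.

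**5. How the grades divide.** Counting every distribution in 1% steps once:

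| Status under the 70% rule | *high* | *moderate* | *low* |
|---|---|---|---|
| Positive consensus | 81.8% | 17.7% | 0.4% |
| Negative consensus | 94.9% | 5.1% | 0% |
| No consensus | 41.2% | 44.7% | 14.0% |

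Equal weighting is an arbitrary choice, and these shares are not a forecast of expert answers. The results in steps 2 to 4 and the value 1.20 do not depend on it.

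**The case against.** The strongest reply is that MADM decides nothing. The 70% rule does, and the median is reported as well. An even scatter has 60% in 1–3 and 40% in 4–5, so it fails the rule, and its *moderate* label cannot make it a recommendation. Low dispersion after a 70% filter is partly to be expected. This stands, and it limits the harm to the strength labels. It does not explain why a printed grade should be unattainable for every negative consensus.

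Four stronger readings are tempting, and the document does not support them.

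- *That total disagreement grades moderate, or that the cut-offs do not discriminate.* A 50/50 split between 1 and 5 has MADM 2.00 and is graded *low*. A 40/0/20/0/40 split has 1.60, also *low*. Without consensus, all three grades occur.
- *That nearly every consensus statement will be published as high.* That would need a model of how experts answer, and an equal-weight count is not one.
- *That the cut-offs were built for a longer scale.* The article does not say what scale the cited study used, so no rescaling can be based on it.
- *That the grades are faulty because a proposition centred on the neutral category can be graded high.* That comes from counting choice 3 as agreement in the 70% rule. MADM measures spread and not direction, so no change of cut-offs would cure it.

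**Conclusion.** The concern holds in a limited form. On this scale the middle grade includes answers with no structure (1.20). The bottom grade is impossible under negative consensus (maximum 1.40 against a threshold of 1.41). Under positive consensus it is open only to near-polarised splits with fewer than 79.5% in 1–3 (maximum 1.60). The top grade admits a panel with 26% in strong disagreement (1.04). These results rest only on the scale, the consensus rule, the MADM definition and the cut-offs as printed.

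For propositions that reach consensus, the three-level grade thus offers two levels on the negative side and little more on the positive side. Which propositions count as agreed is unaffected. The published strength labels would mislead, and that is worth correcting before data are collected.

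**What to change.** Before round 1, revise the strength-of-agreement paragraph in Stage 3 as follows.

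- Reset both cut-offs for a 5-point scale, with a stated rationale, so that the even-scatter value of 1.20 grades *low* and all three grades are attainable among propositions that reach 70%. The first condition makes *low* attainable on both sides, since the maxima there are 1.40 and 1.60.
- Try candidate values on worked distributions. Cut-offs can also be too strict: 40/35/5/10/10 has 75% in 1–2 and a MADM of 0.40 + 0.05 + 0.20 + 0.30 = 0.95. No particular values are proposed here, because the document gives no basis for choosing them.
- State whether all propositions are graded or only those that reach consensus.
- Print the MADM value and the five-category distribution beside each grade.

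The change to the text is small. Fewer statements will be labelled *high*, and the grades will be less comparable with the cited study. Changing the cut-offs after round 1 would cost more, because they would then be chosen with the answers in view.

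### The between-round stability rule does not restrict the comparison to the same respondents, so uneven dropout can take an item near 70% to stable consensus with no rating changed

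*Protocol article*

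**What the plan says.** Two rules in the Protocol article, Stage 3 (Data analysis and consensus grading), decide how a proposition is reported.

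- **Consensus** is a share within one round. It is reached "when the sum of choices 1, 2 and 3 (agree) or 4 and 5 (disagree) reaches 70" per cent.
- **Stability** compares rounds: "Stability of consensus at the end of the eDelphi procedure will be reached if the between round group responses varied by ≤10" per cent. The text does not name the statistic compared, the pair of rounds, the set of respondents, or whether the limit is in percentage points or relative.

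The panel can shrink between rounds. Stage 2b gives the number of people approached ("150–300 ENDOCELL Working Group members will be invited to participate in the survey"), says of dropout that it "cannot be foreseen in advance given the wide range reported (20–60%) in the literature", and adds: "Individuals who wish to opt out of the survey will be removed from subsequent invitations".

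Under Stage 2c there are three rounds, and from round 2 each panellist sees the anonymous group results beside their own previous answer. The same section says: "Each participant in the survey will be assigned a unique identifier to anonymise their responses". Because each person's earlier answer is returned to them, answers can be linked across rounds. The stability rule makes no use of that link.

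**The concern.** A change in an aggregate response between rounds has two possible sources: people changed their ratings, or different people answered. The stated rule cannot separate them. Feedback shows minority raters that they are in the minority and asks them to reconsider. If some of them leave instead, the agree share rises without any change of opinion.

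Items near the 70% line are at stake. There, a modest imbalance in who leaves could decide whether a laboratory step is reported as a stable expert consensus. According to the Recommendation document section, the results feed a statement paper for which scientific societies will be asked for endorsement.

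**Working it through.** The plan gives no figure of its own to reproduce. The check is a direct count in which no rating changes.

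**Inputs from the protocol:** consensus at 70% (Stage 3); stability limit of 10% (Stage 3); cited dropout of 20–60% (Stage 2b).

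**Assumptions:** 300 or 150 people answer the earlier round (the protocol gives invitees only); the agree share at that round is 65% or 60%; the group response is the agree share, meaning ratings 1–3 as in the consensus rule. A dissenter is someone rating 4 or 5.

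**Formula.** Let p be the earlier agree share, a the fraction of agreers lost and b the fraction of dissenters lost. The later share is

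q = p(1 − a) / [p(1 − a) + (1 − p)(1 − b)].

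**Main case, 20% dropout.** Of 300 people, 195 agree (65.0%) and 105 dissent. Sixty leave: 27 agreers (27/195 = 13.8%) and 33 dissenters (33/105 = 31.4%).

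- Later share: (195 − 27)/(300 − 60) = 168/240 = 70.0%, which is consensus.
- Shift: 70.0 − 65.0 = 5.0 points; relative change 70.0/65.0 − 1 = 7.7%. Stable on either reading.
- Dropouts kept at their last rating: 195/300 = 65.0%, no consensus.
- The same 240 people compared with themselves: 168/240 in both rounds, change 0. Pairing repairs the stability measure but leaves the consensus share at 70.0%.
- Earlier-round ratings: 27/60 = 45.0% of those who left agreed, against 168/240 = 70.0% of those who stayed. A comparison of the two groups would reveal the imbalance.

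**How much imbalance is needed** to reach 70.0% from 195/300:

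| Dropout | Agreers lost | Dissenters lost | Later share |
|---|---|---|---|
| 20% | 27/195 = 13.8% | 33/105 = 31.4% | 168/240 |
| 40% | 69/195 = 35.4% | 51/105 = 48.6% | 126/180 |
| 60% | 111/195 = 56.9% | 69/105 = 65.7% | 84/120 |

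The gap needed narrows from 17.6 to 13.2 to 8.8 points as dropout rises.

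**Where the 10% limit does protect.** If only dissenters leave and the whole 20% goes in one transition, reaching 70% needs p ≥ 0.70 × 0.80 = 56%. The shift is then at least 70 − 56 = 14 points (25% relative), and a check across that transition fails.

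**Where it does not.**

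- Loss spread over two transitions, dissenters only, 150 starters with 90 agreeing: 90/150 = 60.0%, 90/134 = 67.2%, 90/120 = 75.0%. The steps are 7.2 and 7.8 points, each within 10 points. On the relative reading they are 150/134 − 1 = 11.9% and 134/120 − 1 = 11.7%, and both fail.
- All loss before round 2, with stability judged on rounds 2 and 3: the shift is 0 and the check passes, whatever the earlier imbalance.

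**The case against.** Four objections have force.

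1. **The mechanism is not documented.** Nothing in the protocol says that minority raters leave. People drop out of a whole survey but dissent on single propositions, so one departure need not push every item the same way. This stands, and it is why the point is about what the rule allows, not what will happen.
2. **The 10% limit catches much one-step attrition.** If dissenters are exactly twice as likely to leave and p is 65%, the later share is 69.2% at 20% dropout (no consensus), and 76.2% at 40% and 90.3% at 60% (shifts of 11.2 and 25.3 points, not stable). Under that pattern the rule is passed only between about 23% and 37% dropout. Likewise, 130/200 becoming 130/180 = 72.2% is 7.2 points but 11.1% relative, so it passes only if the limit means points. This stands too, but the main case above passes on both readings.
3. **A group-level rule follows the declared method.** The Stage 2 section treats analysis of the group response as a binding Delphi principle. Linked respondents are still a group, however, so the principle does not prevent the repair.
4. **This is detail for a fuller document.** The denominator and sensitivity analyses may indeed be specified elsewhere. But the stability criterion itself is stated here, at group level, and the point concerns that stated rule.

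A reader might also infer that the protocol expects 20–60% dropout, or that the consensus rule itself compares different people across rounds. Neither is supported. The range is quoted from the literature with the remark that this study's rate cannot be foreseen, and the 70% criterion is a within-round share. Only the stability rule compares rounds.

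**Conclusion.** The point holds in a conditional form. As written, the stability rule cannot distinguish changed opinions from changed respondents. Within the dropout range that the protocol cites, an item at 65.0% can become a stable consensus at 70.0% with no rating changed.

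This rests on three things: dissenters leaving more often than agreers, a starting share fairly near 70%, and a loss that is not so large and one-sided within the compared transition that it breaches the 10% limit. It also takes the group response to be the agree share, which the protocol does not specify. That different people answer successive rounds is inferred from dropout and opt-outs; the protocol neither says so nor rules it out.

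The documents do not support saying that attrition will produce false consensus, or that most items are at risk. The change is worth making because it affects which items near 70% can be reported as robust.

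**What to change.** 1. State that the 10% means percentage points and that stability compares rounds 2 and 3.
2. Assess stability among participants who rated the item in both of those rounds, linked by the identifier, with the same agree/disagree grouping as the consensus rule.
3. Pairing alone does not correct the consensus share. For each item that reaches consensus, also compare the dropouts' last ratings with the completers' ratings from the same round, and recompute the share with dropouts' last ratings carried forward. Label items that fall below 70% as attrition-sensitive.

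The cost is a few lines of text and a short extra analysis of data already collected. Some items will carry a flag. Carried-forward ratings were not reconsidered in light of later feedback, as the Delphi process intends, so step 3 is a sensitivity check and does not replace the primary rule.
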